### 2.5. Interventions

This study will select patients who meet the study criteria by recruiting them at the hospital. A randomized controlled study will be conducted, in which sodium hyaluronate will be used in the control group and the experimental group will include MT exercise on the basis of the control group. If necessary, the attending doctor may adjust the treatment according to the patient’s condition, and all interventions will be recorded in detail for final outcome analysis. Efficacy assessors are not aware of the study plan, and data statisticians are not involved in study design and implementation. The health of each patient will be assessed before and after the treatment, including observational indicators, and all patients will be followed up by telephone.

#### 2.5.1. Control group.

Patients will be placed in the sitting or supine position, and the knee joint will be kept bent 70° to 90°, sterilized strictly, with sterile towel laid and aseptic operation performed. The lower lateral or inner side of the patella will be used as the conventional puncture point, and the knee joint cavity will be punctured through a 5 mL syringe. If there is joint effusion, it will be drained first, and then 25 mg sodium hyaluronate will be injected (KUNMING BAKER NORTON PHARMACEUTICAI, SALES CO.LTD. [Kunming City, Yunnan Province, China], specification 2.5 mL: 25 mg, CFDA approval number: H20140533); if not, 25 mg sodium hyaluronate can be directly injected into the joint cavity. After injection, help the patient to move the knee joint so that sodium hyaluronate can be evenly coated on the internal surface of the joint. One time/week, 4 times as a course of treatment. Health education should be carried out for patients to avoid acute jumping, walking up and down stairs, climbing mountains and other activities that damage joints, and remind them to pay attention to the warmth of joints as well. Pay attention to communicate with patients, be aware of their psychological and emotional changes, avoid or relieve anxiety, depression, and other adverse emotions of the elderly patients.

#### 2.5.2. Treatment group.

The treatment group will be given MT on the basis of conventional treatment. Manual therapy is jointly completed by 2 experienced doctors, it lasts for about 20 minutes per time, once a day, and lasts for 4 weeks in total.

### 2.6. Outcomes

#### 2.6.1. Observation indicator.

Improvement in joint pain and function is the main observation item, and which is respectively assessed by the visual analogue scale pain score or a comprehensive evaluation commonly using the Western Ontario and McMaster Universities Arthritis Index scores, Lysholm scores, or Bristol scores.

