### 2.4. Sample size calculation

According to the preliminary clinical trial, the total effective rate of MT combined with sodium hyaluronate was 93.4%, and that of sodium hyaluronate was 66.6%. Use PASS15.0 to estimate the sample size, adopt a superiority design, in which α = 0.05, β = 0.2, test power = 0.8, number of cases in experimental group: number of cases in control group = 1:1, boundary value = –0.4. According to the software calculation, the total sample size of the 2 groups was 110 cases. Taking into account the clinical shedding rate of about 10%, a total of 120 cases will be finally included. The included patients will be numbered according to the order of treatment and divided into the treatment group and the control group by completely random method, with 60 cases in each group.

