#### 2.6.2. Efficacy indicator.

Main efficacy indicators: total effective rate: (clinical control + significantly effective number + effective number)/total number of people × 100%. Clinical control: pain and other symptoms disappear, joint activity is normal, integral reduction ≥ 95%; significantly effective: pain and other symptoms disappear, joint activity is not limited, 70% ≤ integral reduction < 95%; effective: pain and other symptoms basically disappear, joint activity is slightly limited, 30% ≤ integral reduction < 70%; and ineffective: no significant improvement in symptoms such as pain and joint activity, integral reduction < 30%.

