### 2.9. Statistical analysis

In this study, SPSS25.0 statistical analysis software (IBM, Amenk, NY) will be used for data analysis. If the measurement data meet the normal distribution, independent-sample *t* test will be used between groups and paired-sample *t* test will be used within groups; if not, non-parametric test will be used and the results will be expressed in quartiles; the count data were tested by chi-square. The incidence of adverse events is compared by chi-square test. *P* < .05 is statistically significant.

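### Two different outcomes are each called main and are not ranked, and the score that defines the responder rate is not named

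*Protocol article*

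**What the plan says.** Four places in the protocol article bear on which outcome decides the trial.

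- **Section 2.6.1 (Observation indicator)** states: "Improvement in joint pain and function is the main observation item, and which is respectively assessed by the visual analogue scale pain score". The sentence goes on to offer, as an alternative, a comprehensive evaluation by WOMAC, Lysholm or Bristol.
- **Section 2.6.2 (Efficacy indicator):** "Main efficacy indicators: total effective rate". This is the share of patients in the top three of four response grades. Each grade combines a description of symptoms and joint activity with a band of percentage reduction in an *integral* (cut-points 95%, 70% and 30%). The section does not say which score the integral is.
- **Section 2.4 (Sample size calculation):** the only effect assumption is on the responder rate: "the total effective rate of MT combined with sodium hyaluronate was 93.4%, and that of sodium hyaluronate was 66.6" per cent, with "α = 0.05, β = 0.2, test power = 0.8".
- **Section 2.9 (Statistical analysis):** t tests or non-parametric tests for measurements, chi-square for counts, and one threshold, P "< .05 is statistically significant".

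The abstract lists the four scales together as observation indicators, along with adverse reactions. It does not mention the total effective rate.

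**The concern.** Adjacent subsections give the label *main* to different outcomes. This is a conflict in what the document states, not detail left to an analysis plan, and a plan written from this protocol would inherit it.

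Two further choices sit underneath. The function scale in 2.6.1 is not fixed. The outcome that was sized cannot be computed from the text, because different scores can put different patients above the 30% cut-point that separates effective from ineffective.

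If these choices are still open once results are visible, the comparison that happens to succeed can be presented as the main one. Its P value then cannot be read at face value, and the conclusion may not concern the outcome the trial was sized for.

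**Working it through.** **Inputs.** Threshold 0.05 per test (2.9). Candidate main measures: VAS, WOMAC, Lysholm and Bristol (2.6.1) and total effective rate (2.6.2), five in all. Response rates 93.4% and 66.6%, α = 0.05, power 0.80, 1:1 allocation (2.4). Correlations between measures are not in the document, so those below are assumptions.

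**1. The plan's own figure.** Section 2.4 gives 110 before dropout. The usual formula for two proportions, without a margin, is

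n per arm = [z(1−α/2)·√(2·p̄·(1−p̄)) + z(power)·√(p1(1−p1) + p2(1−p2))]² / (p1−p2)²

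with p1 = 0.934, p2 = 0.666, p̄ = 0.80 and difference 0.268.

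- Two-sided 0.05, 80% power: (1.960 × 0.5657 + 0.842 × 0.5330)² / 0.0718 = 33.8, so 34 per arm, 68 in total.
- Two-sided 0.05, 95% power: (1.960 × 0.5657 + 1.645 × 0.5330)² / 0.0718 = 54.9, so 55 per arm, 110 in total.
- Using the stated margin, "boundary value = –0.4", as printed gives 8 or 10 in total (one-sided 0.05 or 0.025).

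The stated inputs therefore do not reproduce 110. That is a separate matter and this point does not depend on it. What matters here is that section 2.4 uses the total effective rate and no other outcome.

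**2. False-positive chance if the deciding test is left open.** For k independent tests, each at 0.05, the chance of at least one false positive is 1 − 0.95^k.

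| Tests treated as main | Calculation | Chance |
|---|---|---|
| One fixed in advance | 1 − 0.95 | 5% |
| Two (one from 2.6.1, one from 2.6.2) | 1 − 0.9025 | 9.75% |
| Five (four scales and the effective rate) | 1 − 0.7738 | 22.6% |

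**3. Allowing for correlation.** All five measures concern the same knee's pain and function, so positive correlation is likely. Simulation with equally correlated normal statistics (500,000 draws, two-sided 0.05 each) gives:

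| Assumed correlation | Any of two | Any of five |
|---|---|---|
| 0.3 | 9.5% | 20.9% |
| 0.5 | 9.1% | 18.3% |
| 0.7 | 8.3% | 14.9% |
| 0.9 | 7.1% | 10.2% |

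**4. Direction.** These are two-sided figures. Counting only false results in favour of manual therapy, any-of-five under independence is 1 − 0.975^5 = 11.9%, against 2.5% for one fixed test.

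**5. What is not priced.** The figures count a choice between outcomes. They do not count the choice of score behind the effective rate, because the document gives nothing from which to estimate it.

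**The case against.** The strongest reply is that the intended primary can be inferred. Section 2.6.2 is the only part headed as efficacy, and section 2.4 sizes the trial on that rate alone. Section 2.6.1 is headed as observation, and the abstract uses the same term for a list that includes adverse reactions. On this view the problem is one of labelling. The pointer is real, and it is why the fix is easy to choose. But 2.6.1 still calls pain and function the main item, and the inference does not supply the missing score.

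Several stronger readings are tempting, and the document does not support them.

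- **A free choice among four scales.** The word *respectively* most naturally means VAS for pain and one of the other three for function. What is open is the function scale.
- **Success on any one of five tests.** No such rule is stated. Multiplicity handling is commonly left to an analysis plan, which is not shown, so its absence is not the fault here. The two unranked labels are.
- **22.6% as the expected error.** It needs all five measures to be main and independent, so it is an upper bound.
- **About 40%, by counting a second time point** (1 − 0.95^10 = 40.1%). Section 2.7 describes telephone follow-up for 3 months but does not say the scales or the effective rate are tested again then.
- **A *reduction* that would mean worsening on some scales.** This rests on scoring directions the document does not give, and its own word implies a score that falls with improvement. Only the missing name can be held against it.

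**Conclusion.** The point holds in a limited form. Sections 2.6.1 and 2.6.2 name different main outcomes without ranking them, the function scale is open, and the sized outcome depends on an unnamed score. With a flat 0.05 threshold, the wording permits a choice after the data are seen, although it does not announce one.

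If that happened, the false-positive chance would rise from 5% to 9.75% for two independent main tests, and to at most 22.6% if all five measures were treated as main and independent. With five, it falls to about 18% at a correlation of 0.5 and about 10% at 0.9. These correlations are assumptions, but every case computed is above 5%. The ambiguity should be removed before outcome data are seen, since a choice made afterwards would not be credible.

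**What to change.** 1. In section 2.6, state that the total effective rate is the single primary outcome, at the 4-week assessment, and that the efficacy claim rests on it alone.
2. In section 2.6.2, name before unblinding the one score, falling with improvement, from which the integral reduction is computed. The document does not point to a particular score, so the investigators should name the one they intended.
3. In section 2.6.1, relabel VAS, WOMAC, Lysholm and Bristol as secondary. Once the claim rests on one primary outcome, a formal multiplicity procedure for the secondaries is optional.

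This is rewording only: no extra patients, visits or measurements, and no change to the outcome already sized. The cost is that the scale results become supportive and cannot carry the efficacy claim.

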#### 2.6.2. Efficacy indicator.

Main efficacy indicators: total effective rate: (clinical control + significantly effective number + effective number)/total number of people × 100%. Clinical control: pain and other symptoms disappear, joint activity is normal, integral reduction ≥ 95%; significantly effective: pain and other symptoms disappear, joint activity is not limited, 70% ≤ integral reduction < 95%; effective: pain and other symptoms basically disappear, joint activity is slightly limited, 30% ≤ integral reduction < 70%; and ineffective: no significant improvement in symptoms such as pain and joint activity, integral reduction < 30%.

#### 2.6.3. Adverse events rate.

Including the number of patients who experience any uncomfortable symptoms during treatment (such as dizziness, nausea, etc).

### 2.7. Data collection and management

Data will be collected according to the evaluation criteria before and 4 weeks after the treatment, and each patient was followed up by telephone for 3 months after the end of treatment. It was impossible to collect follow-up information and record the reasons for loss to follow-up. Access to the database is limited to the researchers in this research group.

### 2.8. Study quality control

Throughout the trial, each participant will be monitored for safety. All adverse event occurrences will be referred to the office of the Clinical Research Ethics Committee, which will review the events and determine causal relationship.

### 2.9. Statistical analysis

In this study, SPSS25.0 statistical analysis software (IBM, Amenk, NY) will be used for data analysis. If the measurement data meet the normal distribution, independent-sample *t* test will be used between groups and paired-sample *t* test will be used within groups; if not, non-parametric test will be used and the results will be expressed in quartiles; the count data were tested by chi-square. The incidence of adverse events is compared by chi-square test. *P* < .05 is statistically significant.

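### The 4-week pain and function scores are compared between groups without baseline adjustment; ANCOVA on the baseline already collected would be more precise at no cost.

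*Protocol article*

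**What the plan says.** Section 2.6.1 of the protocol article gives pain and function a leading place: "Improvement in joint pain and function is the main observation item". The instruments named are VAS for pain and WOMAC, Lysholm or Bristol for a composite assessment; they are joined by 'or', so it is not certain that all four will be used. On timing, section 2.7 states: "Data will be collected according to the evaluation criteria before and 4 weeks after the treatment". A baseline value and a 4-week value therefore exist for each score used.

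On the analysis of these scores, section 2.9 states: "If the measurement data meet the normal distribution, independent-sample *t* test will be used between groups". It adds a paired t test within each group. Otherwise, "if not, non-parametric test will be used and the results will be expressed in quartiles". No baseline covariate is named in either branch, and the section does not say whether the between-group test is applied to final scores or to changes from baseline.

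Section 2.6.2 names a separate, binary efficacy measure: "Main efficacy indicators: total effective rate: (clinical control + significantly effective number + effective number)/total number of people × 100". Section 2.4 sizes the trial on that rate, and section 2.9 tests count data by chi-square.

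**The concern.** A patient's pain or function score before treatment is usually among the best predictors of the same score a few weeks later. The plan collects that predictor and leaves it out of the between-group model. This is a method the protocol states, not a detail left open, so an unseen analysis plan does not explain it away. At stake is the width of the confidence intervals for pain and function, and protection against a chance baseline difference between two groups of 60 allocated without any stratification named.

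A second, smaller matter is that section 2.9 places paired tests within each group beside the between-group test, under the same significance threshold. Both groups receive hyaluronate injections and health education, so both may improve whether or not MT adds anything. A paired P value cannot isolate the contribution of MT.

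**Working it through.** **Inputs from the protocol article.** 110 evaluable patients, 55 per group, and 120 recruited (section 2.4); measurement before treatment and at 4 weeks (section 2.7); significance at P < .05 (section 2.9), taken here as two-sided because sidedness is not stated.

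**Inputs assumed.** The correlation ρ between baseline and 4-week score is not given, so 0.3, 0.5 and 0.7 are shown. For the change-score comparison the SD σ is taken as equal at the two times.

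**The plan's own figure.** There is none to reproduce for VAS, WOMAC, Lysholm or Bristol. The 110 in section 2.4 rests on the binary rate. Without a margin, at 80% power and two-sided 5%, that calculation gives 68 in total, so the 110 does not reproduce. That is a separate matter and does not enter the ratios below.

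**Variance of the treatment difference, n per group**
- t test on final scores: 2σ²/n
- t test on change: 2 × 2σ²(1 − ρ)/n
- ANCOVA: 2σ²(1 − ρ²)/n

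Hence ANCOVA/final = 1 − ρ², and ANCOVA/change = (1 − ρ²)/(2(1 − ρ)) = (1 + ρ)/2.

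| ρ | ANCOVA/final | Variance cut | Equivalent total, 120/(1 − ρ²) | ANCOVA/change | Variance cut | Equivalent total, 120 × 2/(1 + ρ) |
|---|---|---|---|---|---|---|
| 0.3 | 0.91 | 9% | 132 | 0.65 | 35% | 185 |
| 0.5 | 0.75 | 25% | 160 | 0.75 | 25% | 160 |
| 0.7 | 0.51 | 49% | 235 | 0.85 | 15% | 141 |

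The equivalent total is the number of patients the unadjusted test would need to match ANCOVA in 120.

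Estimating the covariate slope costs a factor of about 1 + 1/(2n − 4) = 1 + 1/106, or 1%, at 55 per group. This is ignored in the table and leaves the conclusion unchanged.

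**Detectable difference at 55 per group, 80% power**
- Final scores: (1.960 + 0.842) × √(2/55) = 0.534 SD
- ANCOVA, multiplying by √(1 − ρ²): 0.510, 0.463 and 0.382 SD at ρ = 0.3, 0.5 and 0.7
- Change, multiplying by √(2(1 − ρ)): 0.632, 0.534 and 0.414 SD

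ANCOVA is the smallest at each ρ, so the gain does not depend on which t test was intended.

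**Within-group tests.** Suppose both groups truly change by the same amount and each paired test has power p. One is significant and the other not with probability 2p(1 − p): 2 × 0.8 × 0.2 = 32% at p = 0.8, and 2 × 0.5 × 0.5 = 50% at p = 0.5. Both powers are illustrations. A contrast between two paired P values is thus common when MT adds nothing.

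**The case against.** The case for leaving section 2.9 as it is has several parts, and most of them limit the point without removing it.

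- *The t test is valid.* This stands. Under randomisation it holds its type I error rate with or without adjustment. A reader might infer that the planned comparison is biased or invalid; nothing in the protocol supports that.
- *Baseline may already be used.* This stands in part. A reader might infer that baseline is ignored altogether and that chance imbalance carries over in full. That is so only if the test is on final scores. Section 2.6.1 speaks of improvement, which fits change scores at least as well. A change-score test does use baseline, though less efficiently than ANCOVA when ρ is below 1.
- *The outcome that sizes the trial is untouched.* This stands. The total effective rate is binary and partly defined by percentage reduction in score. The point concerns the pain and function scores only.
- *Power may hardly change.* This is fair. If the rates of 93.4% and 66.6% in section 2.4 came from a normal score with equal variances, the implied difference would be about 1.51 − 0.43 = 1.08 SD. At 55 per group, 1.08 × √(55/2) − 1.96 = 3.70, so the plain t test would have power above 99%. This is a rough conversion of a possibly optimistic assumption, but it is a reason to state the gain as precision, with no claimed rise in power.
- *The paired tests are not said to decide anything.* This stands. A reader might infer that efficacy will be read from a significant change under MT and a non-significant one in controls. The plan also states a between-group test and says no such thing, so what remains is a caution on reporting.
- *The normality condition and the quartiles.* A reader might infer that normality will be checked on pooled raw data, or that no effect estimate will be given. Section 2.9 does not say how normality is checked. Quartiles describe presentation, and effect estimates are commonly left to an analysis plan. Neither is pressed here.

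**Conclusion.** The point holds as a free improvement. The planned between-group comparison of the continuous scores is sound but less precise than the collected data allow. Over an assumed ρ of 0.3 to 0.7, the variance reduction from ANCOVA is 9% to 49% against final scores and 35% to 15% against change. The size depends on ρ, which the document does not give, and the change-score figures also on equal SDs at the two times. The direction depends on neither, apart from the small cost of estimating the slope when ρ is near 0 (against final scores) or near 1 (against change).

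The conclusion covers whichever of the four scales are used, at 4 weeks. Section 2.7 does not say which scores, if any, are taken in the 3-month telephone follow-up. The within-group P values call for a caution in reporting; they are not a demonstrated error.

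**What to change.** In section 2.9:

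- Replace the between-group t test on each pain and function score with ANCOVA of the 4-week score on treatment group, with the baseline value of the same score as covariate.
- Report the adjusted mean difference with its 95% CI. This also settles whether final or change scores are analysed.
- State that any conclusion about MT on these scores rests on this between-group comparison only.
- Show within-group changes as descriptive summaries, without paired P values.

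The cost is a few lines of text. The baseline and 4-week values are already collected, SPSS 25.0 fits the model, and neither the sample size nor the analysis of the total effective rate changes. The wording should be fixed before group comparisons are seen.

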## 3. Discussion

CP is one of the common diseases of knee joint. Pain and dysfunction caused by CP severely decreases the quality of life of patients. Currently, the diagnostic standard of CP has not yet formed a unified consensus. There is no effective cure for the treatment of CP, and the effects of surgical treatment which are widely used in clinic, such as cartilage transplantation and total knee replacement, is not superior o non-surgical treatment.^[12,13]^ Moreover, doctors and patients concern constantly about the potential adverse effects of these operation.

At present, MT is one widely used conservative treatment for patients with CP. Manipulative therapy can promote blood circulation and accelerate metabolism, mainly through the following mechanisms to achieve the purpose of treatment: increase the local nutrient supply, and strengthen the “pumping effect” of cartilage tissue itself, which is conducive to the self-repair of the articular cartilage. Eliminate local intra osseous venous stasis, reduce intra ossseous hypertension, and promote absorption of local inflammatory tissue. Exogenous cold pathogen is one of the causes of CP, manipulative treatment can generate heat and disperse cold, and promote local Qi and blood circulation. Promote the mechanical balance of the knee joint, release the adhesion, and improve the stability and functional state of the knee joint.

As far as we know, there has been no standard large-sample clinical study on MT in the treatment of CP, although increasing studies have found that MT has a statistically significant effect on alleviating symptoms of CP with a well-established safety profile. We intend to evaluate its efficacy and safety in a prospective randomized controlled study.
